#### Primary Aim 1: Parenting

To address primary aim 1, we will conduct a multimodal assessment of parental monitoring and parental communication. Specifically, we will use parent and adolescent report measures with strong psychometric properties, as well as an in vivo family assessment task. Prior research suggests that adolescent report of parent behavior is more predictive of adolescent risk behavior than parents’ self-reported behavior [14]. As such, adolescent reports will be used to capture parent behaviors, whereas parent self-report will be used to measure adolescent behaviors.

##### Parent Monitoring Questionnaire

The Parental Monitoring Questionnaire [37] is a 24-item youth and parent-reported measure containing three subscales. We will use the following versions of the subscales to assess dimensions of parental monitoring: child disclosure (parent report), parent solicitation (adolescent report), and parental control (adolescent report). Subscales were reliable in our pilot trial (α=.76-.87) and have been shown to correlate with adolescent mental health problems, deviant peer relationships, and family discord [37].

##### Parent-Adolescent Communication Scale

The Parent-Adolescent Communication Scale [38] is an adolescent and parent reported measure with two subscales. The adolescent-reported version only will be used to assess positive (general family communication) and negative (problems with family communication) aspects of parent-adolescent communication. Subscales had good reliability (α=.71-.92) in our pilot [28] and have been shown to correlate with adolescent engagement in risk behavior [38].

##### Family Assessment Task

The family assessment task (FAsTask) is an audio-recorded family problem-solving task that will be used to provide an in vivo assessment of parenting skills. Three tasks (5 minutes each) will assess parental monitoring and communication: (1) limit setting: parents lead a discussion about a time they had to set a limit); (2) substance use norms: parents lead a discussion on family views about substance use; and (3) monitoring and listening: adolescent leads a discussion about a time they were unsupervised with their peers and parents react. Each item will be rated on a 9-point Likert scale by trained research staff blind to condition using a structured codebook initially developed by Dishion and colleagues [39] and adapted by the research team. Ratings between 1 and 3 will indicate poor parenting skills, ratings >3 to <6 will indicate average parenting skills, and ratings of 6 and above will indicate strong parenting skills. Individual ratings will yield five distinct scale scores: limit setting (10 items), parent substance use beliefs (4 items), parent substance use communication (6 items), adolescent disclosure (7 items), and parental monitoring (9 items).

In the pilot trial, 20% of FAsTasks were double coded with an excellent mean inter-rater reliability of 94%. Moreover, the FAsTask was sensitive to change, with all five subscales demonstrating significant time by treatment condition interactions, favoring Parent SMART+TAU relative to the TAU-only condition in our pilot trial [28].

#### Primary Aim 2: Substance Use

Adolescent substance use will be assessed via the Global Appraisal of Individual Needs-Core (GAIN) [40], a well-validated, structured, comprehensive interview. The GAIN has intake and follow-up versions, which each contain over 100 analyzable scales across eight sections (background, substance use, mental health, physical health, risk behaviors, legal, vocational, and environmental). We do not obtain corroboration from parents or peers since parents often underestimate adolescent use [41-43] and since peer corroboration raises issues of confidentiality and unintentional harm [44]. We will assure adolescents of confidentiality, as self-reported substance use has shown reliability when confidentiality is assured [45].

##### Proportion of Days Substances Used Outside a Controlled Environment (Past 90 Days)

A series of GAIN items will evaluate days of substance use over the past 90 days, as well as days the adolescent was in a controlled environment (eg, residential treatment or justice facility). This will allow calculation of the proportion of days that the adolescent was outside of a controlled environment on which substances were used. The GAIN days of use items have shown excellent comparability [46] to the well-validated Timeline Follow-Back Interview [47,48]. Like the Timeline Follow-back, the GAIN will assess days of alcohol and drug use using a calendar with temporal cues (eg, holidays and special events) to facilitate recall. The proportion of days all substances are used and separate days of binge drinking, marijuana, all other drugs, stimulant, and opioid use will be examined.

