### Specific Aims

**Primary aim 1:** Evaluate the effectiveness of Parent SMART+TAU versus TAU on proximal parenting outcomes. Hypothesis 1 is that, relative to those in TAU, parents receiving Parent SMART+TAU will exhibit greater improvements in parental monitoring and communication at 6, 12, and 24 weeks postdischarge from residential care.

**Primary aim 2:** Evaluate the effectiveness of Parent SMART+TAU versus TAU on distal adolescent substance outcomes. Hypothesis 2 is that, relative to those in TAU, adolescents whose parents receive Parent SMART+TAU will show greater reductions in the proportion of days substances were used outside a controlled environment and substance-related problems at 6, 12, and 24 weeks postdischarge from residential care.

**Secondary aim:** Evaluate the effectiveness of Parent SMART+TAU versus TAU on distal adolescent problem behavior outcomes commonly related to substance use: school problems, externalizing behaviors, sexual risk behavior, and criminal involvement. Hypothesis 3 is that adolescents whose parents receive Parent SMART+TAU will have greater reductions in a range of problem behaviors, including school truancy, externalizing behavior, risky sexual behavior, and criminal involvement at 6, 12, and 24 weeks postdischarge from residential, relative to adolescents in TAU.

**Exploratory aim**: Evaluate the extent to which change in parenting processes mediates change in adolescent substance outcomes. An exploratory hypothesis is that change in parenting processes (ie, communication, monitoring) at 6-weeks postdischarge from residential care will partially mediate primary adolescent substance use outcomes at 12 and 24 weeks.

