### Interventions

#### Residential TAU

TAU consists of the standard residential services offered to adolescents at our partner facility and will be received by families in both conditions. The partner residential treatment program, Rosecrance Health Network, offers residential treatment for adolescents at two locations, one in Rockville, Illinois, and one in Sioux City, Iowa. Length of stay ranges from 2 to 45 days, depending on the adolescent’s level of need and insurance coverage. Adolescents at Rosecrance Health Network receive about 15 hours of educational programming and 25 hours of treatment per week in a predominantly group-therapy model based on dialectical behavioral therapy [30]. Each adolescent is also assigned a primary counselor who checks in with them at least twice per week. Medication management is offered by a nurse practitioner or psychiatrist as needed. Prior to discharge, parents receive standard discharge planning, which consists of a customized relapse prevention plan as well as either a referral to a new outpatient therapy provider or a return to a prior outpatient therapy provider. Families receive referrals to a psychiatrist or local self-help group as indicated. Postdischarge, families are encouraged to phone the intake coordinator for further referrals or support.

Following randomization, parents will be given an educational pamphlet about adolescent substance use, parenting skills, and local community resources, consistent with usual resource provision at the partner site.

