### Study Assessments

Parents and adolescents will complete a baseline assessment shortly after admission to the partner facility. Follow-ups will be conducted by research staff blind to condition at 6, 12, and 24 weeks postdischarge. The baseline assessment will be approximately 90-120 minutes for adolescents and 45-60 minutes for parents; each follow-up assessment will take approximately 60 minutes for adolescents and 30 minutes for parents. If a parent loses physical custody of the adolescent postdischarge, adolescent data will still be collected, and parent data will be classified as missing; administration of the full parent battery will be resumed if the parent regains physical custody. If an adolescent turns 18 over the course of the 24-week follow-up period, then the adolescent will be reconsented as an adult at the next relevant follow-up visit.

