##### Substance-Related Problems Scale

The GAIN substance-related problem scale will be used to obtain a count of substance use symptoms experienced over the past 90 days in line with the latest diagnostic criteria for a substance use disorder [49]. Diagnoses made from this scale have demonstrated good test-retest reliability (κ=.55) [50] and accurately predict independent, blind staff ratings of the presence of substance use disorder (κ=.91) [51]. Reliability in our pilot trial (α=.78) [27] was consistent with prior studies using the same items (α=.76) [51].

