#### Secondary Aim: Adolescent Problem Behavior

GAIN scales will be used to assess common behaviors often linked to adolescent substance use [52-55]; higher scores indicate more problems. Consistent with the substance use scales, these scales will use a 90-day recall. Of note, in the pilot trial, we used an abbreviated version of the GAIN that contained briefer versions of some of these scales; thus, we report psychometric data from the measure validation data trial.

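### The 90-day recall does not fit the 6- and 12-week postdischarge visits: the 6-week score includes days before admission, and about half of the 12-week score was already counted at 6 weeks

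*Protocol article*

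**What the plan says.** Three sections of the protocol article set the recall period. For the proportion of days used: "A series of GAIN items will evaluate days of substance use over the past 90 days". For the substance-related problems scale, the aim is to "obtain a count of substance use symptoms experienced over the past 90 days". For the school, externalizing, sexual-risk and crime scales: "Consistent with the substance use scales, these scales will use a 90-day recall". None of them gives a different window for any visit.

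Under Study Assessments, "Follow-ups will be conducted by research staff blind to condition at 6, 12, and 24 weeks postdischarge", and "Parents and adolescents will complete a baseline assessment shortly after admission to the partner facility". Randomization follows the baseline assessment. Under Residential TAU, "Length of stay ranges from 2 to 45 days". The days-of-use section divides by days outside a controlled environment.

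The Data Analysis Plan fits latent change scores between adjacent visits and adds point-in-time analyses at 6 and 12 weeks. The exploratory hypothesis is that parenting change "at 6-weeks postdischarge from residential care will partially mediate primary adolescent substance use outcomes at 12 and 24 weeks".

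**The concern.** Six weeks is 42 days, so a 90-day question asked then must look back past discharge. Dividing by days outside a controlled environment removes the residential stay. It does not remove the community days before the stay. Those days precede randomisation, so the intervention cannot affect them, and they were already reported at baseline. The article describes no comparable adjustment for the problem count or the secondary scales.

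The windows at 6 and 12 weeks also overlap. Three planned uses of the data are affected:

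- the 6-week contrasts in Hypotheses 2 and 3;
- the baseline-to-6-week and 6-to-12-week change scores;
- the lagged path from parenting change at 6 weeks to substance use at 12 weeks.

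**Working it through.** **The plan's own figure.** The Power section gives 80% power for 0.38 SD with 220 dyads. A two-sided comparison of two means with 110 per arm, alpha .05 and no dropout gives 80.5%. The figure reproduces and is not in dispute.

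**Inputs.** The recall is 90 days, the visits are on days 42, 84 and 168 after discharge, and the stay L is 2 to 45 days. Set discharge at day 0, so that admission is at day -L. Assume no controlled days other than this stay.

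**Windows (visit day minus 90).**

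- 6 weeks: day -48 to day 42.
- 12 weeks: day -6 to day 84.
- 24 weeks: day 78 to day 168.

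**Pre-admission days at 6 weeks.** These number 48 - L. At-risk days number 90 - L, of which 42 are postdischarge.

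| Stay L (days) | Pre-admission days | At-risk days | Share |
|---|---|---|---|
| 2 | 46 | 88 | 52% |
| 10 | 38 | 80 | 48% |
| 30 | 18 | 60 | 30% |
| 45 | 3 | 45 | 7% |

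The longest stay is 45 days, which is less than 48, so the window crosses admission for every stay in the stated range. A baseline taken b days after admission covers the last 90 - b days before admission. With b no larger than L, 90 - b is at least 90 - L, which exceeds 48 - L. All the pre-admission days counted at 6 weeks therefore also lie in the baseline window.

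**Overlap between visits.** The 6- and 12-week windows share days -6 to 42, which is 48 of 90 calendar days. For stays of 6 days or more, 42 of the 84 at-risk days at 12 weeks (50%) were already counted at 6 weeks. For L = 2 the figure is 46 of 88 (52%). The 12- and 24-week windows share 6 days, and the 6- and 24-week windows share none. The 12-week window contains pre-admission days only for stays of 2 to 5 days, and then 4 down to 1 of them.

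**Attenuation at 6 weeks, worst case.** Suppose a 0.38 SD effect acts on postdischarge days only, and the blended score keeps the same SD. The effect becomes 0.38 × 42/(90 - L):

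- L = 2: 0.38 × 42/88 = 0.18 SD.
- L = 10: 0.38 × 42/80 = 0.20 SD.
- L = 30: 0.38 × 42/60 = 0.27 SD.
- L = 45: 0.38 × 42/45 = 0.35 SD.

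**Attenuation when change from baseline is modelled.** The shared days partly cancel, so the SD of the change falls as well. Let w be the pre-admission share. Let r be the correlation of the postdischarge segment with baseline and with the pre-admission segment, and q the correlation of the pre-admission segment with baseline. Give all segments SD 1. Then:

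- Var(change) = w² + (1-w)² + 1 + 2w(1-w)r - 2wq - 2(1-w)r.
- Without contamination, Var(change) = 2 - 2r.
- Retained fraction of the standardised effect = (1-w) × √(2-2r) / √Var(change).

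The documents give neither r nor q. I assume r = 0.3 to 0.5 and q = 0.7 to 0.9. For L = 2 the retained fraction is 65% to 87%, so 0.38 becomes 0.25 to 0.33 SD. For L = 10 it is 70% to 90%, or 0.27 to 0.34 SD. Adjusting for baseline as a covariate gives similar fractions.

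**Mediation timing.** At 12 weeks, days 0-42 of the outcome fall in the period over which the 6-week parenting change itself accrues. That is 42 of 84 at-risk days for stays of 6 days or more. At 24 weeks the outcome window starts at day 78, wholly after day 42.

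**The case against.** The strongest defence concerns consequence, because the day counts follow directly from the stated figures. Use before randomisation is balanced between arms in expectation, and the urn balances on planned length of stay. Any distortion of the 6-week contrast is therefore towards no effect. The Power section's 0.38 SD refers to time-by-condition interactions and is not stated as a 6-week contrast, and shared days partly cancel in change scores. All of this stands. It rules out reading the worst-case figures as the expected loss.

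A reader might go further and infer that Primary Aim 2 as a whole is invalid, or that the mediation test runs backwards in time. The documents support neither. The 24-week window is wholly postdischarge, and the 12-week window holds at most 4 pre-admission days. For the 12-week outcome the mediation fault is partial concurrency, in an exploratory aim, and the 24-week path is correctly ordered. Nor does the article give the Aim 1 parenting measures a 90-day window.

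A reader might also assume that the calendar interview already allows rescoring by date. The article says only that the calendar aids recall. It does not say that dated use is recorded.

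What the defence does not remove is that part of the stated 6-week outcome cannot respond to treatment, by an amount that varies with length of stay.

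**Conclusion.** The concern holds for the 6-week substance and problem contrasts, the two early change scores and the 12-week mediation path. Between 7% and 52% of at-risk days at 6 weeks precede admission, depending on stay, and about half of the 12-week window repeats the 6-week window. These counts rest only on the stated recall, visit times and stay range, and on there being no other controlled days.

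The loss of effect at 6 weeks is real, but its size is uncertain. The worst case takes 0.38 SD to 0.18 SD for a 2-day stay. When change from baseline is modelled, 0.25 to 0.33 SD is more plausible under the assumed correlations. No arm is favoured, and the 24-week outcome and its mediation path are essentially sound.

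**What to change.** **Proportion of days used.** Ask and score both use days and controlled days since discharge at 6 weeks (days 0-42) and since the 6-week visit at 12 weeks (days 43-84). Keep 90 days, or days 85-168, at 24 weeks. Divide each by the days outside a controlled environment in that interval. Because this outcome is already a proportion of days at risk, it tolerates windows of different length.

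**Symptom and behaviour counts.** Keep the standard 90-day version for the 24-week analysis. Add a since-discharge version at 6 weeks and a since-last-visit version at 12 weeks. Compare the arms at each of these visits with the baseline score as covariate, and do not read the result as raw change from the 90-day baseline count.

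**Mediation.** Test the lagged path on use in days 43-84 and on the 24-week outcome.

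**Cost.** The changes are to interview prompts and scoring, and are best settled before data collection because symptom counts cannot readily be re-dated later. Early windows become shorter and noisier, and scoring departs from the standard 90-day form. The early counts cover a shorter period than baseline, which strains measurement invariance over time, and the reliability figures cited for the 90-day scales would not carry over to the shorter versions.

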##### Substance-Related Problems Scale

The GAIN substance-related problem scale will be used to obtain a count of substance use symptoms experienced over the past 90 days in line with the latest diagnostic criteria for a substance use disorder [49]. Diagnoses made from this scale have demonstrated good test-retest reliability (κ=.55) [50] and accurately predict independent, blind staff ratings of the presence of substance use disorder (κ=.91) [51]. Reliability in our pilot trial (α=.78) [27] was consistent with prior studies using the same items (α=.76) [51].

##### Urine Drug Screens

Urine drug screens will be used to corroborate self-reported abstinence and gauge under-reporting of substance use in adolescents. Urine screens will be collected via 8-panel dip urine screens at the 12-month and 24-month follow assessments (75% testing rate in our pilot trial). Samples will be tested for metabolites of marijuana, cocaine, amphetamines, methamphetamines, barbiturates, phencyclidine, opiates, and benzodiazepines.

#### Secondary Aim: Adolescent Problem Behavior

GAIN scales will be used to assess common behaviors often linked to adolescent substance use [52-55]; higher scores indicate more problems. Consistent with the substance use scales, these scales will use a 90-day recall. Of note, in the pilot trial, we used an abbreviated version of the GAIN that contained briefer versions of some of these scales; thus, we report psychometric data from the measure validation data trial.

##### Behavioral Complexity Scale

This scale counts 33 externalizing behaviors, including symptoms of conduct, inattention, and hyperactivity. The full scale has good test reliability for total symptoms (*r*s=.7-.8) and strong internal consistency (α=.94) [40].

##### School-Related Problems

This four-item scale counts school-related problems, including truancy, chronic tardiness, poor grades, and cutting class. The full scale has demonstrated significant associations with adolescent employment problems, substance use, and cumulative stress in prior studies [56].

##### Risky Sexual Behavior

This three-item scale evaluates the number of risky sex-related behaviors, including sexual activity with multiple partners, unprotected sex, and sex while under the influence of alcohol or drugs. The full scale has demonstrated concordance with adolescent substance use and mental health problems in prior studies [40].

##### General Crime Scale

This 31-item scale assesses the number of behaviors the adolescent engaged in indicative of general conflict, as well as property, interpersonal, and drug crime. Test-retest reliability of the full scale has been shown to be excellent with strong internal consistency (α=.90) [40].

##### Covariates: Demographics

Parent and adolescent sociodemographics will be assessed and controlled for as covariates. Parents will complete a routine sociodemographic form. Adolescents will complete the GAIN Background section, which collects routine sociodemographic variables including age, sex, gender identity, ethnicity, race, and grade in school. Items in other GAIN sections indicate the adolescent’s history of substance use or mental health treatment utilization, data that will be used to control for treatment received.

### Data Analysis Plan

#### Overview

The data analysis plan contains periodic data quality checks, early generation of analysis variables, and mock study table generation to provide a check on completeness of study data. The study statistician will be blind to treatment conditions and follow a protocol established a priori.

Hypotheses will be tested with a latent change score modeling [57] approach estimated within a structural equation modeling framework [58]. The structural equation modeling framework allows direct estimating and testing hypotheses of interest, including treatment effects and mechanisms of action across multiple outcome variables. Compared to latent growth modeling, latent change score modeling is flexible (ie, not structured) with respect to the shape of the trajectory of change. This approach avoids misspecification of the change trajectory and allows for the testing of mediation hypotheses (exploratory aim). As a mixed repeated measures approach based on maximum likelihood estimation, the model produces unbiased effect estimates and standard errors under the missing at random assumption. The missing at random assumption is less restrictive than the missing completely at random assumption that is implicit in complete case or carry-forward methods for missing data and consistent with the intent-to-treat principle [59]. We will focus on intent-to-treat analyses to optimize rigor and account for the fact that families randomized to Parent SMART may engage in passive activities, such as lurking in the app or reading push notifications. Supplementary completer analyses will assess effects among those who complete at least two telehealth coaching sessions and two Parenting Wisely modules. Analyses will also control for contact time (eg, number of modules completed, number of posts in the app, and number of sessions attended) as a covariate in analyses of primary and secondary outcomes. The full analysis plan will be coded and executed on collected data at the end of Year 1 to identify errors so final analyses can be completed quickly.

Primary aims 1 and 2 and the secondary aim compare trajectories of change using data from baseline, 6, 12, and 24 weeks follow-up on parenting processes, adolescent substance use, and adolescent problems, respectively. These aims will be evaluated in latent change score models with separate change effects for each of the adjacent time points [57]. For each aim (primary aims 1-2 and secondary aim), multiple outcomes are specified. For example, primary aim 1 specifies parental communication (two subscales) and parental monitoring (three subscales). Primary aim 2 includes days of substance use as well as problems related to substance use. A single latent variable at each time point will be used to define a composite outcome reflecting shared covariance among the multiple outcome indicators. Measurement invariance will be tested over time, and noninvariance will be assumed if necessary. “Point-in-time analyses” will be conducted to assess preliminary effects at 6 weeks and then at 12 weeks.

The exploratory aim examining potential mediators will be evaluated by bringing outcome models together in a single multivariate model. The exploratory hypothesis posits that positive changes in parenting processes at 6 weeks will be related to reductions in adolescent substance use and adolescent problems at 12 and 24 weeks. A bivariate change score model will evaluate change in parenting processes and change in adolescent substance use and related problems simultaneously and introduce a residual covariance term describing the association of change in parenting and change in adolescent outcomes. Time lagged regression coefficients will then be applied to test whether a change in parenting processes at 6 weeks leads to lower adolescent substance use and adolescent problems at 12 and 24 weeks. Examples of such an approach to evaluating mediation and moderation effects in the context of randomized trials can be found in McArdle and Prindle [60].

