#### Power

The study’s primary and secondary aims were specifically powered to detect small to medium effect sizes on the Time*Condition interactions, based on: (1) the effect sizes detected in our pilot trial, which were small to medium in size, and which matched the proposed population in terms of severity; and (2) the effect sizes of the online parenting program on parenting processes detected in prior clinical trials, which were medium to large [24,32,33]. With a sample size of 220 dyads, we will have 80% power to detect a 0.38 standard deviation effect size or larger with a type I error risk of .05.

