### Potential Strengths and Limitations

This pragmatic effectiveness trial is characterized by a number of strengths. Most notably, Parent SMART is a novel technology-assisted intervention that was developed based on extensive formative research with parents, adolescents, and residential treatment staff and is supported by encouraging data from a rigorous pilot randomized controlled trial. This study will build upon the successful pilot trial by conducting a fully-powered evaluation of the intervention’s effects on parental monitoring, parent-adolescent communication, adolescent substance use, and adolescent behavioral outcomes. Moreover, this study will move beyond simply testing the effectiveness of the intervention by specifying and examining putative mediators of change. Finally, the Parent SMART intervention is highly scalable: it augments an off-the-shelf intervention with a parent networking app and telehealth sessions that require limited training to deliver. Future work will seek to test different delivery models of Parent SMART to support long-term sustainability: (1) delivery by trained residential staff who bill for services, and (2) delivery by outside vendors, purchased as part of a technology package paid for by the residential center as part of the bundled rate.

In addition to these strengths, several limitations should be considered. A key limitation is that the Parent SMART+TAU and TAU conditions do not offer an equivalent dose of contact time. As a result, favorable results associated with Parent SMART may be attributable to a higher overall dose of treatment. This decision was made because our goal was to assess whether the package intervention was a feasible, acceptable, and effective adjunct to residential services delivered under real-world conditions. A related limitation is that Parent SMART is a bundled, multicomponent intervention, which will limit the ability to determine which aspects of the intervention (ie, the computer program, parent networking app, telehealth sessions) are driving observed effects. To mitigate these limitations, we will carefully control for each type of contact time (eg, number of telehealth sessions completed, time spent in the app, number of parenting skills modules completed) in analyses of primary and secondary outcomes.

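### Adjusting the primary and secondary models for contact time, which exists only in the Parent SMART arm, replaces the intention-to-treat effect and cuts power from 80% to about 30%

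*Protocol article*

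**What the plan says.** In the Protocol article, Data Analysis Plan, Overview, the authors commit to a focus on intent-to-treat analyses. They label a completer analysis as supplementary and then write "Analyses will also control for contact time (eg, number of modules completed, number of posts in the app, and number of sessions attended", with these counts entering as covariates for the primary and secondary outcomes. Potential Strengths and Limitations repeats the commitment, "we will carefully control for each type of contact time", as the remedy for two stated limitations: unequal contact between arms and a bundled intervention.

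Table 1 and the Parent SMART section list Parenting Wisely, the forum and coaching only under the experimental condition. The Residential TAU section gives control parents standard services and a pamphlet.

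Three other statements bear on the point:
- Overview: "The study statistician will be blind to treatment conditions".
- Covariates: Demographics, on treatment-utilisation history: "data that will be used to control for treatment received".
- Power: "we will have 80% power to detect a 0.38 standard deviation effect size or larger with a type I error risk of .05". The Power section does not mention contact-time adjustment.

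**The concern.** Modules, posts, app time and sessions are the intervention as received. They are not baseline confounders. Because they do not vary in TAU, their slopes are estimated only among Parent SMART families. The arm coefficient then becomes the difference between TAU and a Parent SMART family projected back to zero on every counted activity. This has four consequences.

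- **Estimand.** Any benefit delivered through the counted activities is moved out of the arm effect. An intervention that works as intended can look ineffective.
- **Precision.** Arm and contact time are strongly collinear, so the standard error rises even when the estimate is unbiased.
- **Confounding.** Engagement is self-selected. If it is related to outcome for other reasons, the projection to zero carries that bias into the arm effect, in either direction.
- **Purpose.** The adjustment cannot equalise dose between arms, because TAU has no contact variation to adjust against.

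Table 1 also shows forum and program use running to 12 weeks, so some contact can follow the 6-week outcome it would adjust. A lesser point is that structural zeros identify the arm to a statistician who is meant to be blind. Both primary aims rest on these models.

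**Working it through.** **Inputs**
- From Study Design and Power: 220 dyads, 1:1 (110 per arm), 0.38 SD, 80% power, alpha .05.
- From Coaching Sessions: pilot sessions mean 2.7 (SD 1.1), with 29 of 30 parents initiating. From the coach training section: 78 sessions in all. Counting the non-initiator as zero gives 78/30 = 2.6, SD about 1.19.
- From Online Parent Skills Program: modules mean 3.8 (SD 2.3).
- From Networking Forum: 16 + 50 = 66 posts over 30 parents = 2.2 per parent.
- Assumed: SD of posts 2.2-4.4; correlations between contact measures 0-0.7 for two covariates and 0-0.5 for three.

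**The plan's own figure.** SE = √(2/110) = 0.135. Power for 0.38 SD, two-sided, is 80.5% (normal) or 80.1% (t-test). The required size is 109 per arm, 218 in total. The stated 80% therefore reproduces, with no contact-time covariate in the model.

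**Variance inflation.** Let the contact covariates be zero in TAU, with mean vector m and covariance S in Parent SMART. With n per arm, the adjusted arm coefficient has variance (σ²/n)(1 + m'S⁻¹m) for the projected Parent SMART mean, plus σ²/n for TAU. Relative to 2σ²/n:

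VIF = 1 + m'S⁻¹m / 2

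- Sessions: 1 + (2.7²/1.1²)/2 = 1 + 6.02/2 = 4.0
- Sessions, non-initiator as zero: 1 + (2.6²/1.19²)/2 ≈ 3.4
- Modules: 1 + (3.8²/2.3²)/2 = 1 + 2.73/2 = 2.4

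For sessions alone, the SE is 0.135 × √4.0 = 0.27. Power is Φ(0.38/0.27 − 1.96) = Φ(−0.55) = 29%.

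| Contact covariates in model | VIF | Power if 0.38 SD survives | Detectable effect at 80% power | Dyads for 80% (218 × VIF) |
|---|---|---|---|---|
| None | 1.0 | 80% | 0.38 SD | 218 |
| Modules | 2.4 | 45% | 0.58 SD | 516 |
| Sessions | 3.4-4.0 | 29-33% | 0.70-0.76 SD | 741-875 |
| Sessions + modules | 3.4-5.4 | 23-33% | 0.70-0.88 SD | 744-1173 |
| Sessions + modules + posts | 3.7-5.9 | 21-31% | 0.72-0.92 SD | 799-1282 |

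**What the coefficient estimates.** This was checked by least-squares simulation: 4,000 runs, 110 per arm, sessions rounded and limited to 0-4, modules to 0-9, correlation 0.5 assumed. The adjusted columns are for sessions alone; adding modules changes them little.

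| Truth | Unadjusted estimate, rejection | Adjusted estimate, rejection |
|---|---|---|
| 0.38 SD, unrelated to dose | 0.38, 80% | 0.38, 27% |
| 0.38 SD, proportional to sessions | 0.38, 79% | 0.01, 5% |
| Half constant, half proportional to sessions | 0.37, 79% | 0.19, 10% |
| No effect; engagement correlates 0.3 with outcome | 0.00, 5% | −0.72, 75% |

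In the last row the bias takes its sign from the engagement-outcome correlation, so it can imitate either harm or benefit.

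**The case against.** The strongest reply is that the adjusted analysis may be meant as an addition. The sentence contains the word 'also' and follows a supplementary analysis, and neither the description of the latent change score models nor the Power section lists contact time. This does not rescue the text. Only the completer analysis is labelled supplementary. The contact-time sentence covers the primary and secondary outcomes without qualification, and the limitations section presents it as the remedy for unequal dose. Even on the generous reading, the plan would produce two treatment estimates without saying which one tests the hypotheses.

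Some narrower objections stand:
- The power loss depends on which covariates enter and on pilot engagement carrying over. Modules alone would leave 45%.
- An estimate near zero is the extreme case, in which all benefit is linear in sessions. With half dose-driven, it is 0.19 SD.
- The Overview notes passive use such as reading notifications, which the listed counts miss. The contrast is therefore at zero measured use, not zero exposure.
- The slopes do carry some within-arm information on which components matter. That belongs in a separate dose analysis.
- The control for treatment received may concern pre-admission history only. It is a problem only if care after randomisation is included, so it is a query. The Conclusions section says only that the intervention might promote continuing care.

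**Conclusion.** The concern holds. As written, the primary and secondary models condition on post-randomisation use of the intervention, so their arm coefficient is not the intention-to-treat effect named in the same paragraph. At pilot engagement, with sessions in the model, the standard error roughly doubles and power falls from 80% to about 21-33%, even if the full 0.38 SD survives. If benefit comes through the sessions, the estimate shrinks toward zero. If engagement is related to outcome for other reasons, the arm effect can be spurious.

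The estimand problem needs only that TAU contact is zero. No sentence says so, but it follows from how the arms are defined. The power figures rest on pilot engagement, assumed correlations and an assumed SD for posts. They also use a two-arm regression in place of the treatment path in the latent change score model. This should be corrected before any comparison by arm is run.

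**What to change.** 1. Remove contact time from every model that yields a primary or secondary treatment effect, in both the Data Analysis Plan and the limitations section.
2. State that all covariates in those models are measured before randomisation (for example the urn factors and the baseline outcome), and that treatment history means care before the index admission.
3. Report modules, posts, app time and sessions descriptively by component.
4. Address dose in a separate analysis labelled exploratory or secondary. It can be a within-arm dose-response analysis in Parent SMART, read as non-randomised, or a complier-average causal effect model.
5. Keep contact-time data from the blinded statistician until the main models are final.
6. Let the unequal-contact limitation stand as a limitation, since covariate adjustment cannot remove it.

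The cost is wording in the analysis plan. No data collection, sample size or procedure changes, and the planned 80% power for 0.38 SD is no longer eroded by this adjustment.
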